### Randomization and Masking

Participants will be randomized to the 2 treatment groups at a ratio of 1:1 using stratified simple randomization. The randomization list will be generated using a random number generator in a Microsoft Excel spreadsheet. Participants will be stratified into 2 age groups (7-9 years and 10-12 years). This is a single-masked study in which examiners are masked to the treatment allocation. Allocation concealment will be ensured using sequentially numbered, opaque, sealed envelopes. The envelopes will be opened by the designated unmasked investigators in numerical order only after the participants are enrolled. To maintain masking, access to the randomization list will be limited to the trial steering committee; study management committee; statistician; and unmasked investigators designated to handle randomization, allocation, and delivery of group assignments. These individuals will not be involved in participant enrollment or data collection.

### Procedures

Mass emails to the staff of Hong Kong Polytechnic University, advertising posts on social media (Facebook and Instagram), and referrals from parents or guardians who are already participating in the study will be used to recruit participants. Parents or guardians and their children will be invited to the Optometry Research Clinic for a screening visit to confirm their eligibility. Informed consent and assent will be obtained upon confirmation of fulfillment of the inclusion criteria.

Successfully enrolled participants will be randomly allocated to 1 of the 2 arms after baseline measurement. Delivery of spectacles and a light therapy lamp will be arranged 2 weeks after the baseline visit. Training will be provided to participants and parents or guardians on how to set up and use the light therapy lamp at home. The participants in both treatment groups will be asked to return 1 month after the intervention for aftercare appointments to ensure that there are no allergic reactions to atropine or adverse events associated with the light therapy lamp. Participants will also be asked to return for regular follow-up visits with the study ophthalmologist for dispensing of 0.01% atropine.

Data collection will be conducted every 6 months from the baseline visit up to 24 months. Baseline measurements will include demographic data; medical and medication history; visual acuity; tests for strabismus, autorefraction, and keratometry; pupil size; amplitude of accommodation; accommodative lag; subjective and objective refraction with and without cycloplegia; intraocular pressure; choroidal thickness; external and internal ocular health; peripheral refraction; and axial length via the IOLMaster 500 (ZEISS) and other ocular biometry (eg, corneal curvature, corneal thickness, anterior chamber depth, and lens thickness) via the Lenstar LS 900 (Haag-Streit AG). In addition, questionnaires on visual performance, daily activities, and compliance will be administered at the 6-, 12-, 18-, and 24-month visits. A SPIRIT schedule of the study is shown in Table 1.

**Table 1. T1:** Schedule of enrollment, interventions, and assessments.

Timepoint	Baseline	1 month	6 months	12 months	18 months	24 months
Enrollment						
Allocation	✓					
Interventions						
Single treatment: atropine & single vision lenses		✓	✓	✓	✓	✓
Combination treatment: bright light therapy & atropine & single vision lenses		✓	✓	✓	✓	✓
Assessments						
Primary outcome: cycloplegic objective refraction	✓		✓	✓	✓	✓
Secondary outcome: axial length	✓		✓	✓	✓	✓
Other outcomes: intraocular pressure, accommodative functions, pupil size, and peripheral refraction	✓		✓	✓	✓	✓
Safety outcomes: treatment compliance, visual performance, and adverse events		✓	✓	✓	✓	✓

### Interventions

Eligible participants will be randomized to 1 of 2 groups: (1) bright light therapy and atropine group (high-intensity lamp for bright light therapy, 0.01% atropine eye drops twice a day [1 drop in the morning and 1 drop at night before bedtime], and single vision spectacle lenses) and (2) atropine group (0.01% atropine eye drops twice a day [1 drop in the morning and 1 drop at night before bedtime] and single vision spectacle lenses). Participants will stay in these groups for 24 months.

#### Bright Light Therapy

During bright light therapy, participants are exposed to an LED lamp on a daily basis as they perform near visual tasks (eg, homework, reading, or using a computer). Each participant will be provided with a lamp (model DL93011, Carex Health Brands; Figure 2) commonly used in previous psychiatric studies [21]. It emits 4000-K glare-free white light rated at 10,000 lux at 30 cm from the screen to the cornea. The spectral radiance of the lamp can be found in Figure 3. The polycarbonate diffuser of the unit blocks UV light with a cutoff of approximately 400 nm. Participants will use the lamp at home and be given standardized verbal instructions, including viewing distance, viewing angle, and duration of use. The lamp head should be angled at approximately 15 degrees from vertical, with the center of the lamp head located 30 to 55 cm from the participant’s eye. Participants will be asked to use the unit for at least 45 minutes per day (not more than 120 minutes per day) and 7 days per week. This dosage is chosen because clinical trials using similar protocols (30-60 minutes per day) have reported effective remission of depressive symptoms and well-tolerated treatment [22]. Participants may choose when to use the lamp during the day and to skip the treatment on days when they have already had more than 2 hours of outdoor activities under sunlight. To avoid causing insomnia, participants will be advised not to use the lamp within 3 hours prior to bedtime. They will also be trained on how to use the unit properly. There will be a network-enabled device attached to the lamp to monitor and record the duration of treatment, working distance, and ambient light illuminance. To promote compliance, researchers will make phone calls to participants (or their guardians) regarding lamp use during the first month of the trial and to provide guidance when needed. All lamps will be returned to investigators at the end of the study.

**Figure 2. F2:**
[figure not shown]
Light therapy lamp with monitoring sensor attached underneath.

**Figure 3. F3:**
[figure not shown]
Spectral radiance of the light therapy lamp measured using a spectroradiometer (model S-R3; Topcon Technohouse Co).

#### Atropine

Sterile, unpreserved, unidose 0.01% atropine eye drops will be provided to parents or guardians for administering to the participants as 1 drop in the morning and 1 drop at night before bedtime (twice a day) for 24 months. Each vial will be disposed of daily to prevent microbial contamination. An ophthalmologist will perform an ocular health assessment at the atropine dispensing visit, 1 month later, and every 6 months thereafter.

#### Single Vision Spectacle Lenses

The single vision spectacles, prescribed according to the cycloplegic subjective refraction, will be provided to participants in both treatment groups. The lenses are made of plastic, with a refractive index of 1.6. Participants will be instructed to wear the spectacles full time. At each follow-up visit, an update in prescription will be made if either of these criteria is fulfilled: (1) an increase in myopia of 0.50 D (spherical overrefraction) or more or (2) habitual visual acuity equal to or worse than 0.20 logMAR.

### Outcomes and Measurements

The primary and secondary outcome measures will be changes in cycloplegic autorefraction in spherical equivalent refraction and axial length, respectively, measured every 6 months over 2 years from baseline. Other outcomes include peripheral refraction, pupil size, choroidal thickness, amplitude of accommodation, accommodative lag, corneal curvature, noncontact intraocular pressure, visual performance questionnaire, and treatment compliance (assessed via the frequency and/or duration of the use of atropine and bright light therapy).

### Compliance

Compliance with spectacle wear will be monitored through questionnaires at 6-month intervals. Compliance with light therapy will be monitored through 2 means. First, participants or their parents or guardians will be instructed to record the treatment duration daily using a mobile app. Second, a cloud-enabled monitoring sensor attached to the bottom of each light therapy lamp (Figure 2) will be used to collect data on background lighting, working distance, and use time for each participant. Compliance with atropine eye drops will be monitored through a self-reporting log through the aforementioned mobile app. Additionally, custom-built medicine boxes with cloud-enabled sensors will be randomly distributed to 20 participants in the atropine group. The sensors will collect data on the time and frequency of the actions of opening and closing the boxes, providing another measure of compliance.

Compliance data will be analyzed monthly, and participants with poor compliance will be reminded to follow the treatment modality via WhatsApp messages.

### Safety Considerations

The side effects of bright light therapy have been extensively researched in both psychiatric patients and healthy adults [22,23]. No ocular abnormalities have been found with either short- or long-term bright light therapy [24]. Some commonly reported side effects include headaches, eye strain, blurred vision, and nausea, but these were mild and temporary [23,25]. Bright light therapy is generally considered a safe and well-tolerated treatment [22].

A meta-analysis of the safety of low-dose atropine revealed that no major adverse events were detected in all 4 studies included. Side effects of atropine include photophobia, blurred near vision, lower accommodation amplitude, and a larger pupil size [26]. Overall, low-dose atropine is considered a safe treatment for myopia control [26,27].

The visual functions, ocular health, and visual and nonvisual symptoms of both treatment groups will be strictly monitored at every follow-up visit. Adverse events, causally related or not to the study intervention, will be recorded and classified by severity. These include but are not limited to reduced visual acuity, visual disturbances, eye strain, eye infection or allergic reaction, photophobia, headache, or nausea. Participants will receive appropriate medical care for any clinically significant adverse events. Any serious adverse events will be reported to the Institutional Review Board of Hong Kong Polytechnic University within 48 hours. All adverse events will be followed up on until adequate resolution. An investigator may withdraw a participant from the study if any clinical adverse event or situation occurs such that continued participation in the study would not be in their best interest.

### Data Management Plan

The source documents consist of signed consent and assent forms, printouts of ophthalmic investigations (eg, autorefractor and tonometer), and electronic case report forms (eCRFs). All paper documents will be stored in lockable cabinets. All study data will be recorded on standardized eCRFs and stored in an online REDCap (Research Electronic Data Capture; Vanderbilt University) [28] database, in which the server is built and protected under a secure campus network. Access is restricted to authorized study investigators, each with a unique account, ID number, and password. Only specific forms can be viewed and modified based on the investigators’ assigned roles. Anonymized participant identifiers will be used for any data entry and documents uploaded to REDCap. An unmasked investigator must review and approve each eCRF after all data have been entered. An independent monitor will check the presence and correct date of all signed consent forms. The monitor will sample approximately 10% of all randomized participants to check correct data collection and data entry for the key points of this study.

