A recent 1-year–long randomized clinical trial by He et al [41] provides supporting evidence for this hypothesis. In their study, the axial elongation and spherical equivalent refraction progression in the twice-daily group (n=36) were 34% and 53% lower, respectively, than in the once-daily group (n=34). There were no clinically significant differences between the 2 groups in safety parameters, including accommodation amplitude, pupil diameter, and intraocular pressure. The study proposed in this paper, with a larger sample size and longer follow-up, will provide additional insights into optimizing the balance between efficacy and safety in low-dose atropine treatment for myopia control.

The strengths of this study include its prospective, randomized design and the use of masked examiners. The primary limitation of this study is the lack of masking of participants. The study duration is only 24 months due to budget constraints, so longer-term results will not be available. In addition, while the effectiveness of bright light therapy is examined in this study, further research is still needed to determine the optimal light level. Whether the benefit, if any, would apply to patients with different characteristics also remains to be assessed.

The results of this study will be disseminated at scientific conferences and in peer-reviewed, indexed journals in the fields of optometry and ophthalmology.

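### Outcome eCRFs are approved by an investigator who knows the arm, which weakens the protection that examiner masking gives the outcome data

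*Protocol article*

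**What the plan says.** Three parts of the protocol article bear on this.

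- **Randomization and Masking** states the extent of masking: "This is a single-masked study in which examiners are masked to the treatment allocation". The randomization list is open to the steering and management committees, the statistician, and "unmasked investigators designated to handle randomization, allocation, and delivery of group assignments". Of all of these it says: "These individuals will not be involved in participant enrollment or data collection".
- **Data Management Plan** states where the data go, "All study data will be recorded on standardized eCRFs and stored in an online REDCap", and who signs them off: "An unmasked investigator must review and approve each eCRF after all data have been entered". The same section counts the eCRFs among the source documents, next to consent forms and instrument printouts. It describes form-level access, "Only specific forms can be viewed and modified based on the investigators’ assigned roles", and an independent monitor who checks data collection and entry for about a tenth of randomized participants.
- **Discussion** lists masked examiners among the strengths and adds: "The primary limitation of this study is the lack of masking of participants".

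**The concern.** Families know which arm they are in, because one arm has a lamp and the other does not. Masking of the people who measure is therefore the only masking the trial has. Its purpose is to let refraction and axial length enter the database uninfluenced by knowledge of the arm.

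A mandatory sign-off by someone who knows the arm comes after that point and partly undoes the benefit. An implausible reading might be looked at harder in one arm than in the other, even in good faith. Any such asymmetry would act on the primary outcome, the change in cycloplegic spherical equivalent, and on axial length. It would also touch measures that depend more on judgement, such as accommodative lag, questionnaire answers and the grading of adverse events.

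This is not a detail left to an unseen document. The article states the rule and gives no exception.

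**Working it through.** The main check is a reading of the text. The only arithmetic is a count of the visits exposed.

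**1. Does the rule cover the outcome forms?** All study data are recorded on eCRFs, and the approval rule applies to each eCRF. Together these include cycloplegic refraction and axial length. No carve-out appears.

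**2. Does the approver know the arm?** Yes, since the rule calls for an unmasked investigator. The text does not say whether this is one of the investigators designated to handle allocation, but that does not matter here: the approver knows the arm either way.

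**3. How does this fit with Randomization and Masking?** That section keeps holders of the list out of enrollment and data collection. Approval after entry is not plainly data collection. However, the eCRF is itself listed as a source document, so approving it comes close. The two sections are in tension and need to be reconciled.

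**4. How many visits are exposed?**
- Participants (Sample Size Calculation): 2 × 67 = 134, which matches the stated total.
- Refraction and axial length are scheduled at baseline, 6, 12, 18 and 24 months (Table 1). Allocation follows the baseline measurement (Procedures), so four visits come after randomisation.
- Upper bound: 134 × 4 = **536** visits.
- With the planned 20% loss, 0.20 × 134 = 26.8, or about 27 participants. If all 27 left before month 6, the count would be 107 × 4 = 428. If all missed only month 24, it would be 536 − 27 = 509. The timing of loss is an assumption, and these are the two extremes.

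**5. How much do the stated safeguards cover?**
- Monitoring: 10% of 134 is about 13 participants, or 13 × 4 = 52 visits at full attendance. About 121 participants, or 121 × 4 = 484 visits, fall outside the sample.
- Printouts: the autorefractor and tonometer are named as examples. A printout would expose an altered value if someone compared the two. For items without a printout, the eCRF would be the only one of the listed source documents to hold the value.
- Form-level roles: these cannot shield outcome forms from a person who must approve each of them. They do show that the access split needed for a remedy already exists.

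**6. Effect on the design figures.** None. Who reviews the forms enters no sample-size, power or significance calculation.

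**The case against.** The best case for the plan has four parts.

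- **Approval comes after measurement and entry.** Nothing in the text passes the allocation back to an examiner. This stands. A reader might infer that the trial's only masking is broken, but the document does not support that.
- **The text says review and approve, and no more.** It does not say that the approver may query, change or reject a value, and the rules on queries and audit trails are commonly kept in a fuller document. This also stands. Selective correction is a risk that the step leaves open, not a power that the article grants. For the same reason, and because review is not clearly collection, calling the two sections flatly contradictory goes too far.
- **The primary outcome is an objective instrument reading with a retained printout and some independent monitoring.** This stands in part. It makes a large undetected distortion unlikely, but the stated monitoring reaches about one participant in ten, and the more subjective measures lack the same backing.
- **An unmasked approver may be deliberate.** Lamp-compliance data reveal the arm, and unmasked review keeps those data away from examiners. This is a fair reason for unmasked review of those forms, but not of the outcome forms.

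Two further inferences are tempting. One is to count 134 × 5 = 670 visits. Baseline values are measured before any arm exists, and the article does not say when baseline forms are approved, so they are left out here. The other is that the statistician's access to the list means analysis decisions will be made with arms known. Coding of arms until database lock is normally settled in the statistical analysis plan, which is not shown, so nothing follows from the article on that.

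**Conclusion.** The point holds at moderate severity. As written, a person who knows the arm must sign off every outcome record, up to 536 post-randomisation visits, or between 428 and 509 under the planned loss. This weakens the protection that examiner masking gives the outcome data, and it is in tension with the rule that keeps holders of the allocation out of data collection.

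The conclusion assumes that the approval rule means what it says, that is, every form and an approver who knows the arm. If the word for an unmasked approver is a slip for a masked one, the concern falls away, but the text still has to be corrected. The size or direction of any bias cannot be derived from the document, and none is claimed.

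**What to change.** - **Rule:** have every eCRF that holds outcome measurements approved by a masked team member other than the one who took the measurement. The second condition matters because the only masked staff the article describes are the examiners, who should not approve their own readings.
- **Access:** use the existing form-level REDCap roles to confine unmasked review to allocation, dispensing and lamp-compliance forms. If any form mixes outcome measurements with content that reveals the arm, split it.
- **Records already approved:** recruitment ended in February 2024 and data collection runs to April 2026, so a change of wording cannot reach past approvals. Have a masked person check those outcome records against the source printouts, where kept, before database lock.
- **Text:** reword Data Management Plan and Randomization and Masking so that they agree on what people who know the allocation may do with outcome data.

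The cost is a small reassignment of review work, a change of role settings and one retrospective check. No participant procedure, sample size or analysis changes.

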### Statistical Analyses

The latest version of the SPSS software (IBM Corp) will be used for statistical analyses. This study will use the same statistical approach as that used in the previous phase 1 study [15]. Data from the right eyes will be used for analyses. The normality of the data will be examined using the Kolmogorov-Smirnov test. Demographic and optometric data will be presented as means and SDs or as numbers and percentages as appropriate. The chi-square test (or, if appropriate, the Fisher exact test) and one-way ANOVA will be performed to compare baseline between-group differences in demographics (age and sex). Changes in primary, secondary, and other outcomes at different time points will be analyzed using a mixed-effects model for repeated measures, which includes fixed effects for the treatment group, time, the interaction between group and time, and covariates including age and baseline myopia. If statistically significant differences in baseline demographic characteristics between arms are found, these will also be adjusted for.

The progression of myopia over 2 years will be calculated as the difference in cycloplegic autorefraction in spherical equivalent refraction and axial length between the baseline and the 2-year visit. The relative treatment effect in each arm will be determined by dividing the difference in myopia progression between the treatment group and the control group in the phase 1 study [15] by myopia progression in the control group and then multiplying by 100%. Additionally, the absolute treatment effect [29] will be presented to facilitate comparison with other studies. Multiple regression analysis will be used to identify factors associated with myopia control effectiveness.

All analyses will follow the intention-to-treat approach. Missing values of outcome variables and covariates will be replaced using a multiple imputation procedure with 10 sets of imputations assuming missingness at random. Sensitivity analyses for the primary outcomes include (1) complete-case analysis and (2) per-protocol analysis. All analyses will be 2-tailed, with a significance level of 5%.

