### Sample Size Calculation

The sample size is estimated based on the 2-year change in refractive error in the 0.01% atropine treatment group (−0.64, –0.44 to +0.44 D) from a previous myopia control study [20]. Assuming that, over 2 years, combination treatment is more effective than 0.01% atropine alone by 0.25 D, which is considered a clinically significant change, 56 participants per group will be required. This sample size will enable the demonstration of a statistically significant difference between the 2 groups at a 5% significance level with 85% power. The sample size for each study arm will be adjusted to 67 per arm assuming a 20% loss to follow-up. As a result, a total sample size of 134 participants will be recruited for this study.

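### The primary model gives age and baseline myopia one coefficient for all visits of a cumulative outcome, which under-adjusts the 24-month contrast and costs some efficiency

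*Protocol article*

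**What the plan says.** Under Statistical Analyses, "Changes in primary, secondary, and other outcomes at different time points will be analyzed using a mixed-effects model for repeated measures". The fixed effects are listed as "fixed effects for the treatment group, time, the interaction between group and time, and covariates including age and baseline myopia". One interaction is named, and it is group by time. The covariance structure is not given.

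Under Outcomes and Measurements, the primary outcome is the change in cycloplegic spherical equivalent refraction and the secondary outcome is the change in axial length, both "measured every 6 months over 2 years from baseline". Two-year progression is defined in Statistical Analyses as the "difference in cycloplegic autorefraction in spherical equivalent refraction and axial length between the baseline and the 2-year visit".

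The Sample Size Calculation targets the 2-year contrast. It assumes that "combination treatment is more effective than 0.01% atropine alone by 0.25 D" and concludes that "56 participants per group will be required" for 85% power at the 5% level, before allowance for loss to follow-up.

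**The concern.** Every child's change is zero at baseline. If younger or more myopic children progress at a different rate, the resulting difference in accumulated change widens from visit to visit. A single coefficient per covariate says instead that the whole difference is present at 6 months and stays the same size to 24 months.

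The model must compromise across visits. When the fit lets variance increase with time, the early visits carry most weight because change varies least there. The common coefficient then falls well below the covariate's effect at 24 months. Covariate-related variance that could have been removed stays in the residual at the visit that matters most, and the standard error of the 24-month group contrast is larger than it need be.

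**Working it through.** **Inputs from the documents.** Difference 0.25 D; n = 56 per arm; two-sided 5%; 85% power. The SD of 2-year change is taken as 0.44 D, read from the value printed as "0.01% atropine treatment group (−0.64, –0.44 to +0.44 D". Visits are at 6, 12, 18 and 24 months.

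**Assumptions not in the documents.** Age and baseline myopia together explain R2 = 0.05-0.30 of the variance in 24-month change. Their effect grows linearly with time. Measurement-error SD is 0.05-0.15 D, with the baseline error shared by all changes. The remaining variation between children follows random slopes, Brownian motion or an equal mix. Data are complete.

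**Step 1: the plan's own figure.** n = 2(1.960 + 1.036)² × 0.44² / 0.25² = 55.6, so 56 per arm. With SE = 0.44 × √(2/56) = 0.0832, normal-approximation power is Φ(0.25/0.0832 − 1.96) = 85.2%. The stated figure is reproduced using the unadjusted SD.

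**Step 2: what a common coefficient keeps.** With complete data, the adjusted 24-month contrast is the raw mean difference minus the common coefficient times the covariate imbalance. Let f be the common coefficient divided by the true 24-month effect. Then

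- share of the variance reduction kept = 1 − (1 − f)²
- effective 24-month SD = 0.44 × √(1 − R2 × share kept).

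**Step 3: the size of f.** With b the covariate effect at the four visits, proportional to (0.25, 0.5, 0.75, 1), and S the residual covariance, generalised least squares gives the common coefficient 1'S⁻¹b / 1'S⁻¹1.

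- Unstructured covariance: f = 0.03-0.39, so 5-63% is kept.
- Compound symmetry: f is the simple average, (0.25 + 0.5 + 0.75 + 1)/4 = 0.625, so 1 − 0.375² = 86% is kept.

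**Step 4: power with 56 per arm (unadjusted 85.2%).**

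| R2 | Covariates crossed with visit | Common coefficient, unstructured | Points forgone | Common coefficient, compound symmetry |
|---|---|---|---|---|
| 0.05 | 87.0% | 85.3-86.3% | about 1-2 | 86.7% |
| 0.10 | 88.7% | 85.4-87.3% | about 1-3 | 88.2% |
| 0.20 | 91.9% | 85.7-89.4% | about 3-6 | 91.1% |
| 0.30 | 94.9% | 86.0-91.6% | about 3-9 | 93.7% |

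One cell in full: R2 0.20, mixed process, measurement-error SD 0.10 D. Here f = 0.23 and the share kept is about 40%. The SD is 0.44 × √(1 − 0.20 × 0.40) = 0.422 D, the SE 0.0798 and the power 88.0%. With full adjustment the SD is 0.44 × √0.80 = 0.394 D, the SE 0.0744 and the power 91.9%.

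**Step 5: simulation check** (56 per arm, 1,500 trials per scenario, R2 0.20, measurement-error SD 0.10 D, unstructured fit). Power with a common coefficient against visit-specific coefficients was:

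- random slopes: 84.5% against 91.3%, 22% of the variance reduction kept
- mixed process: 88.5% against 92.9%, 38% kept
- Brownian motion: 89.5% against 92.4%, 53% kept.

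The mean group contrast was within 0.002 D of the truth in every scenario run.

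**The case against.** **The text is condensed.** An article gives the model in one sentence, says the covariates are those it includes, and refers to the phase 1 approach, which is not shown. Interaction terms may be in the full plan. That stands as a caveat. Still, the sentence names the model's interaction and crosses time only with group, so it states a form. If the full plan differs, saying so closes the point.

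**A reader might infer that most of the covariates' precision is lost.** The documents do not support that. It holds for some assumed processes under an unstructured covariance, but up to 63% is kept under others and 86% under compound symmetry. Neither the covariance structure nor R2 is stated.

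Compound symmetry is not a good way out, however. It assumes equal variance at 6 and 24 months. Under the assumed processes the pooled variance would be about 48-71% of the 24-month variance. A nominal 1.96 cut-off would then act as 1.96 × √0.48 = 1.36 to 1.96 × √0.71 = 1.65, a two-sided error of about 17% to 10%.

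**A reader might infer bias.** Suppose the age SD is 1.6 years, the age effect at 24 months is 0.087-0.151 D per year (R2 0.10-0.30), and the fitted common slope is 0.022-0.041. A 0.5-year difference in mean age would then leave 0.5 × (0.087 − 0.022) = 0.03 D to 0.5 × (0.151 − 0.041) = 0.055 D uncorrected. But 0.5 years is near the 95% limit of chance, 1.96 × 1.6 × √(2/67) = 0.54 years. Over randomizations the contrast is unbiased, and this variation is already in the standard error. Counting it as a separate harm would count the same loss twice.

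**Nothing promised is lost.** This stands. The sample size uses the unadjusted SD, and formula power with a common coefficient never falls below 85.2% at 56 per arm. The simulated 84.5% is within simulation error of that figure.

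**Conclusion.** The point holds as one of efficiency. As listed, the model under-adjusts the 24-month contrast whenever age or baseline myopia affects progression rate. Under the unstructured-covariance assumptions above, the power forgone is about 1-3 points at R2 0.10 and 3-6 points at R2 0.20. Under compound symmetry it is under 1 point at either value. The exact loss cannot be fixed from the documents, because it depends on an R2, a residual process and a covariance structure that they do not give. The calculation treats the two covariates jointly, so it does not say how much each contributes. The validity of the randomized comparison and the planned power calculation are not in question. The change is worth making because it is nearly free and acts at the visit on which the trial is sized.

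**What to change.** Before database lock, state for the primary and secondary outcomes that:

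- time is a categorical visit (6, 12, 18, 24 months);
- the fixed effects are group, visit, group by visit, age, age by visit, baseline and baseline by visit, where baseline is the baseline value of the outcome analysed (refraction for refraction, axial length for axial length);
- the within-child covariance is unstructured;
- the treatment effect is the group contrast at 24 months from this model.

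The cost is a few lines of plan wording and 2 × (4 − 1) = 6 extra fixed-effect parameters per outcome. No new data are needed. If the full plan already has these terms, it is enough to say so.
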